## Abstract

**Background:**

The use of high-flow oxygen therapy (HFOT) compared with standard low-flow oxygen therapy (LFOT) may improve outcomes in people with oxygen-dependent chronic respiratory failure (CRF). The primary aim of this multicentre trial was to evaluate HFOT in addition to LFOT, compared with regular LFOT in people with CRF due to chronic obstructive pulmonary disease (COPD) or interstitial lung disease (ILD).

**Methods:**

Registry-based randomised controlled trial (R-RCT) of people on LFOT for CRF due to COPD (*n* = 270) and ILD (*n* = 40), at ten Swedish secondary care centres within the Swedish Register for Respiratory Failure (Swedevox). People with ongoing LFOT are randomised in a 1:1 ratio to standard treatment with LFOT (control) or LFOT with added HFOT during nighttime and at the patient’s discretion daytime (intervention). HFOT is provided using the ResMed Lumis HFT system and the AcuCare HFNC Cannula. Primary outcome is time to first hospitalisation or death up to 1 year in people with COPD. Secondary outcomes include symptoms, health-related outcomes (HRQL), health-economics, adverse events, and to explore the effects of HFOT in people with CRF due to ILD. Outcome data will be obtained from national registries and from patient questionnaires at 3 and 12 months.

**Discussion:**

This R-RCT will combine the advantages of a prospective randomised trial and large clinical national registries to improve the evidence-based use of long-term oxygen therapy. Recruitment started in June 2024 and is ongoing.

**Trial registration:**

ClinicalTrials.gov, ID: NCT06247397. Registered 2024–02–07.

**Supplementary Information:**

The online version contains supplementary material available at 10.1186/s13063-026-09488-8.

## Introduction

### Background and rationale {6a}

Long-term oxygen therapy is an established treatment that improves survival in people with chronic respiratory failure and severe hypoxemia due to chronic obstructive pulmonary disease (COPD) and interstitial lung disease (ILD) [1–4].

Oxygen therapy is usually administered through a nasal cannula using low flows (often 0.5–4 L/min), called low-flow oxygen therapy (LFOT), employing cold and dry gas [3, 4]. People with LFOT often experience side effects such as nose and upper/lower airways dryness, ulcerations, secretions, and phlegm stagnation, potentially contributing to a higher risk of exacerbations, hospitalisations, deterioration of health-related quality of life (HRQL), and premature death [5–8]. In addition, LFOT is the second most expensive health-care event (after hospitalisations) driving costs in people with respiratory disease such as COPD [9].

High-flow oxygen therapy (HFOT) is an emerging treatment alternative that provides humidified and heated gas via special equipment and a nasal cannula, specifically designed for high flows, at high flow rates (often 20–60 L/min). Beneficial physiological effects of HFOT include more effective oxygenation, improved wash-out of carbon dioxide, decreased dehydration, increased mucociliary clearance, improved respiratory mechanics, and higher treatment adherence [10, 11].

HFOT is believed to reduce the anatomical dead space and increase the wash out carbon dioxide [12]. Especially in COPD, dead space contributes to exercise intolerance and impaired ventilation, and subsequently HFOT may increase endurance and improve oxygen saturation during exercise [13].

The humidification and heating of the gas in HFOT is a very important component. Standard oxygen therapy affects the efficiency of the respiratory epithelium by decreasing humidity and temperature, which may lead to altered viscosity of respiratory secretions, bronchoconstriction, and reduced cilia movement and velocity of the mucociliary clearance [14, 15]. Impaired mucociliary clearance, in turn, is known to be associated with reduced lung compliance, increased airway resistance, and higher breathing work, and causes a risk of mucus plugging, alveolar atelectases, and infection [16, 17].

Finally, HFOT can also lead to improved pulmonary mechanics by reducing work of breathing, increasing lung compliance, improving gas exchange, and improving ventilation homogeneity [10].

Although HFOT is an open system with some leakage, it still provides a low positive airway pressure (PEP) of about 3 cm H2O, which may reduce inspiratory effort and work of breathing [11, 18]. In both healthy people and in patients with COPD, IPF, and IVA, HFOT has been shown to reduce respiratory rate, increase tidal volumes, decrease breathlessness, and improve ventilation homogeneity assessed using electrical impedance tomography, compared with low flow [11, 19].

As for the subjective experience, the most important positive effect of HFOT in acute hypoxic respiratory failure seems to be that HFOT compared with LFOT is associated with less dryness and less breathlessness [11, 20]. Reported side effects of prolonged HFOT after surgery and intubation are skin damage and erythema in the nasal philtrum, but this risk still seems lower than with NIV or CPAP [21, 22].

There are no obvious negative physiological effects of HFOT. However, it is important to emphasize that in spite of a small PEP, there is also still no evidence for replacing non-invasive ventilation as the gold standard treatment in acute hypercapnic respiratory failure [18, 19]. It is also of great interest that HFOT applied to tracheostomy makes no differences compared with LFOT, suggesting that the beneficial effect is mainly on the upper airways [23].

During the COVID-19 pandemic, HFOT was widely used with improved clinical outcomes among people with acute respiratory failure [24], and there is now an increasing interest in using HFOT for long-term treatment. In people with COPD and chronic hypoxic respiratory failure, a randomised controlled trial (RCT) from Denmark has reported a reduced risk of exacerbations, decreased breathlessness, and improved exercise tolerance and HRQL compared with regular LFOT [25]. In people with COPD and combined stable hypoxemia and hypercapnia, two Japanese studies reported a reduced exacerbation rate and improved HRQL [26, 27].

However, robust evidence from adequately powered multicentre studies evaluating critical outcomes such as mortality, hospitalisation rates, and health-economic impacts is notably lacking, underscoring the need for this trial. Furthermore, no trial has explored effects of HFOT in people with other diagnoses than COPD, such as ILD.

## Objectives {7}

The overall objective of this trial is to improve the evidence-based treatment in people with chronic respiratory failure due to COPD or ILD.

The primary objective is to test the effect of added HFOT as compared to usual LFOT on time to first hospitalisation or death during 1 year in people with oxygen-dependent chronic respiratory failure (CRF) due to COPD.

The secondary objectives are as follows:To evaluate treatment effects on other outcomes including respiratory symptoms, HRQL measured via validated questionnaires, and health-economics, and to explore the effects of HFOT in people with CRF due to ILDTo assess adverse effects of HFOT compared with LFOT

## Trial design {8}

HILOT is a registry-based, randomized clinical trial (R-RCT) with the aim of investigating whether one of two treatment arms is superior to the other. There are two parallel groups, where the first treatment arm is existing standard treatment with LFOT at least 15 h/day. The second treatment arm also consists of oxygen at least 15 h/day, where LFOT is replaced by HFOT minimum during night-time. During daytime, the patient may choose between HFOT and LFOT.

People with ongoing LFOT are randomised in a 1:1 ratio to standard treatment with LFOT or LFOT with added HFOT during nighttime and at the patient’s discretion daytime (Fig. 1). Randomisation will be performed between the treatment groups using a central, computerised, online procedure, stratified by main reason for the ongoing LFOT (COPD or ILD) and by study centre, in blocks of 2–8 participants. The randomised treatment group will not be blinded for the participants or the study staff for practical reasons but will be blinded for the statistician before the lock of the study database.

**Fig. 1 Fig1:**
[figure not shown]
Trial outline. Abbreviations: COPD = Chronic Obstructive Pulmonary Disease, HFOT = High-Flow Oxygen Therapy, ILD = Interstitial Lung Disease, LFOT = Low-Flow Oxygen Therapy, LTOT = Long-term Oxygen Therapy

## Methods: participants, interventions, and outcomes

### Study setting {9}

Participants are recruited from ten secondary care centres in Sweden, connected to Swedevox: Umeå, Uppsala, Stockholm, Karlstad, Örebro, Linköping, Trollhättan, Gothenburg, Karlskrona, and Lund/Malmö. All sites and participants are connected to the oxygen arm of the Swedish National Registry of Respiratory Failure (Swedevox). Swedevox is a high-quality registry with 85–90% coverage, and with validated prospective national data collection on patients starting LTOT since 1987 [5, 28]. Swedevox data have previously successfully been used for registry-based controlled trials as well as cohort studies [29–32]. In the present study, the register is used for recruitment and baseline data. People registered in Swedevox due to ongoing therapeutic LFOT due to COPD or ILD since ≥ 28 days which is prescribed to be used ≥ 15 h per day are invited for screening. The primary study population is planned to be 270 people with CRF due to physician-diagnosed COPD. We also aim to include an exploratory cohort of 40 people with CRF due to ILD.

### Eligibility criteria {10}

Inclusion criteria are as follows:Age 40 years or older.Ongoing LFOT, prescribed for at least 15 h per day, and for a minimum of 28 days as registered in Swedevox.COPD or ILD as the main underlying reason for LFOT.Oxygen concentrator as a stationary oxygen source in the home including night-time.Body mass index (BMI) < 35 kg/m^2^ (to reduce potential confounding related to obesity-associated respiratory issues and sleep apnea).

Exclusion criteria are as follows:Current or previous treatment with home HFOT.Current treatment with home mechanical ventilation.Current treatment with home continuous positive airway pressure (CPAP).Hospitalised during the last 2 weeks.Current smoking or contact with flames.Self-reported average use of the LFOT < 15 h per day (24 h).PaCO2 (breathing air at rest) > 8 kPa.Strong clinical suspicion of obstructive sleep apnoea or obesity hypoventilation syndrome (as judged by the responsible staff).Inability to participate in the study procedures (as judged by the staff).Not eligible for continuing LFOT due to other reason (as judged by the staff).Expected survival less than 3 months (as judged by the staff).

### Who will take informed consent? {26a}

Participants will receive oral and written study information by the local primary investigator (PI), including that taking part is entirely voluntary and that they can withdraw from the study whenever they want without this affecting the usual care. Written informed consent will be obtained before study assessments and randomisation.

### Additional consent provisions for collection and use of participant data and biological specimens {26b}

Not applicable.

## Interventions

### Explanation for the choice of comparators {6b}

The intervention in this study is added nocturnal HFOT during sleep and at the patient’s discretion daytime, with standard LTOT treatment (LFOT) the rest of the time up to a minimum of 15 h oxygen per day. The comparison arm is continued usual care with LFOT at least 15 h/day, in accordance with clinical routine.

The investigational device used in this study is the system ResMed Lumis HFT and the AcuCare HFNC Cannula (Ref. Clinical Manual, © 2021 ResMed. 288280/4 2021–05). Lumis HFT delivers warmed and humidified respiratory gases to spontaneously breathing patients through a high flow nasal cannula, the AcuCare HFNC. The operating flow range of Lumis HFT is 15–40 L/min, and tube temperature and humidity can be adjusted. The Lumis HFT user guide, including technical specifications, is provided as supplemental material.

### Intervention description {11a}

At the start of Lumis-HFT, the device is connected to a power source. The humidifier is filled with water to the marker of maximum water level and placed at the side of the Lumis-HFT device, and the air hose is connected to the device. The ordinary LFOT concentrator is set in an off mode and is connected to the Lumis-HFT device. The Lumis HFT device is started and heated for 10–20 min. The device temperature is started at 34 °C, with an oxygen flow at 20 L/min and humidification at level 3 based on standard clinical guidelines to optimise patient comfort and adherence. After applying the cannula on the patient, the treatment is started by pushing the on-button at the Lumis HFT device, followed by starting the oxygen concentrator.

The oxygen flow default is 20 L/min, but if tolerated by the patient, the flow may be increased up to 30 or a maximum of 40 L/min. The oxygen fraction is titrated to reach the previously aimed saturation for standard LFOT, according to the Swedevox recommendations corresponding to PaO2 ≥ 8.0 kPa. The temperature aim is 37 °C, but may be lowered back to 34 or even 31 °C. If needed, the humidification may also be lowered to level 2 or increased to level 4 or 5.

### Criteria for discontinuing or modifying allocated interventions {11b}

Participants will be withdrawn if the trial treatment is judged to be harmful or carry unacceptable risk for harm, or at any time at the discretion of the participant. The trial treatment can be changed or discontinued at the discretion of the responsible physician or participant, which is not a reason for withdrawal from the trial.

Trial participation is completely voluntary and participants who wish to do so can withdraw at any time. Participants who want to withdraw will be asked which trial procedures they want to withdraw from, and whether they consent to be included in parts of the follow-up, including the registry-based endpoints.

### Strategies to improve adherence to interventions {11c}

At the telephone follow-up at one week (range 4 days) after randomisation, and in the questionnaires at 3 and 12 months, the patient is asked to report average daily oxygen and HFOT utilisation. Data on HFOT utilisation will also be collected from centres using the remote home-monitoring system AirView and from staff-reported questionnaires at 3 and 12 months (each to be filled in within ± 4 weeks). The information will be used to assess whether additional follow-up visits or calls are needed to improve adherence.

### Relevant concomitant care permitted or prohibited during the trial {11d}

This is a pragmatic academic trial investigating the addition of high-flow oxygen to standard treatment. All concomitant care is in accordance with clinical practice.

### Provisions for post-trial care {30}

After completion of the trial, the responsible clinician and the participant will decide if they would like to continue with HFOT treatment according to clinical routines. All participants are insured within the general Swedish Patient Insurance.

### Outcomes {12}

The primary outcome is time to first hospitalisation or death from all causes during 1 year after randomisation in people with COPD (at 1 year, assessed using nationwide registries).

Secondary outcomes are as follows:Time to first all-cause hospitalisation or all-cause death in people with ILD (at 1 year after randomisation, assessed using nationwide registries).Rate of hospitalisations or death from all causes (at 1 year).Hospitalisation rate from all causes (1-year and long-term).Hospitalisation rate from respiratory disease (1-year and long-term).Hospitalisation rate from cardiovascular disease (1-year and long-term).Number of hospitalised days (all-cause/respiratory disease/cardiovascular disease) (at 1 year and long-term).Number of admissions to intensive care unit (ICU) (at 1 year and long-term).Number of days in ICU care (at 1 year and long-term).The mortality rate from all causes (at 1 year and long-term).The mortality rate from respiratory disease (at 1 year and long term). The mortality rate from cardiovascular disease (at 1 year and long-term).Time to first exacerbation after randomisation, defined as time to first dispensed antibiotics and/or oral corticosteroids, emergency department visit, or hospitalisation for exacerbation (at 1 year).Number of exacerbations of all severity (at 1 year).Incidence of cardiovascular disease (at 1 year and long-term).Need for home mechanical ventilation (at 1 year and long-term).Rate of LFOT withdrawal (at 1 year and long-term).Safety and tolerability (adverse events at 3 and 12 months).Cost-effectiveness (at 1 year and long-term).HRQL (at 3 and 12 months).Symptoms (dyspnea, cough, phlegm, upper airway symptoms, fatigue, including nighttime symptoms, sleep) (at 3 and 12 months).Factors associated with the net clinical benefit of the HFOT, including the daily usage time.Patients’ perceptions of oxygen therapy and related factors.Adverse events as safety endpoints.

The secondary outcomes will be evaluated in the following populations: (1) people with COPD; (2) people with ILD; and (3) all people. All analyses will be performed primarily by randomised treatment group (intention to treat; ITT), and secondarily by treatment used (per protocol; PP).

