## Statistical methods

### Statistical methods for primary and secondary outcomes {20a}

A detailed statistical analysis plan (SAP) will be established and published in collaboration with a biostatistician before the lock of the database for the primary analysis and before performing each secondary analysis.

The population for efficacy analyses is defined as all randomised people who did not withdraw their consent to be included in the outcome analyses (ITT population). The population for safety analyses is defined as all randomised people who started their randomised treatment (safety population). All analyses will be performed primarily by randomised treatment group (ITT) and secondarily by treatment used (PP).

Data will be summarised using mean with standard deviation and median with range and interquartile range for continuous variables with normal and skewed distributions, respectively. Categorical variables will be expressed as frequencies and percentages. Differences between groups will be analysed using Student’s *t*-tests (for normally distributed continuous outcomes), chi2 tests (for dichotomous outcomes), and Wilcoxon’s rank sum test (for ordinal and non-normally distributed data).

Outcomes will be compared between the treatment groups using multivariable regression models, expressed as point estimates with 95% confidence intervals. The primary outcome will be analysed using Cox proportional-hazards regression. Secondary outcomes will be analysed using appropriate statistical methods: logistic regression for categorical outcomes, Cox regression for standard survival analysis, Fine–Gray regression for competing risk scenarios, and linear regression for continuous outcomes, ensuring robust and context-appropriate analysis. Mixed regression models with random effects will be used to analyse outcomes measured in the same individual at several time points to account for repeated measurements. The outcome analyses will be adjusted for age and sex, the stratification variables, number of hospitalisations during the 12 months before baseline, and time from starting LFOT in Swedevox. Statistical significance will be defined as a two-sided *p*-value < 0.05.

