### Methods for additional analyses (e.g. subgroup analyses) {20b}

People with COPD and ILD will be analysed separately. If the projected sample size is not reached, all randomised people can be analysed as a secondary analysis, which will be detailed in the SAP.

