## Dissemination plans {31a}

The project will result in several publications in peer-reviewed international journals on: (1) trial design; (2) primary and main secondary outcomes; (3) health economic analysis; (4) additional secondary outcomes including in people with ILD; (5) correlational analyses of predictors of net clinical benefit; (6) systematic review and meta-analysis with all available data in this field; and (7) long-term registry follow-up. The results of the study are expected to be implemented in national and international clinical guidelines on home oxygen therapy.

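### Correlating daily HFOT use, or any factor among HFOT users only, with outcome cannot show who benefits from HFOT; effect modification should be estimated across both arms

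*Protocol article*

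**What the plan says.** All references are to the protocol article.

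- **Outcomes {12}** includes among the secondary outcomes "Factors associated with the net clinical benefit of the HFOT, including the daily usage time". Net clinical benefit is not defined. The same section makes analysis by randomised group primary for all analyses, with analysis by treatment used second.
- **Dissemination plans {31a}** gives this work a paper of its own: "correlational analyses of predictors of net clinical benefit".
- **Trial design {8}** states "There are two parallel groups", with 1:1 allocation.
- **Strategies to improve adherence {11c}** shows how usage is obtained. After randomisation, at one week, 3 months and 12 months, "the patient is asked to report average daily oxygen and HFOT utilisation". Staff questionnaires add to this, as do device downloads at centres with remote monitoring.
- **Statistical methods {20a}** says "Outcomes will be compared between the treatment groups using multivariable regression models", lists adjustment covariates, and defers detail to a SAP before each secondary analysis.
- **Methods for additional analyses {20b}** says "People with COPD and ILD will be analysed separately". No treatment-by-factor interaction is mentioned there or elsewhere.
- **Discussion** reports that in the two-centre pilot phase most participants allocated to HFOT gave it up, chiefly because discomfort and noise disturbed sleep. Starting settings, cannula size and patient information were then changed.

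**The concern.** The benefit of HFOT to one person is the difference between that person's outcome with it and without it. Each participant here is followed on one allocation, so the difference is never seen. What can be estimated is whether the HFOT-versus-LFOT contrast differs between levels of a baseline factor, and that needs both arms.

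Daily HFOT use does not fit this scheme. It is not a baseline variable, and LFOT participants have no corresponding value, so it cannot enter an interaction with randomised arm. A simple association with outcome has to be made among people using HFOT, and there three things are mixed with any benefit:

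- tolerance, since people who cope with the device may differ from those who do not;
- prognosis, since sicker people may use it less, or more;
- reverse causation, since admission or death itself cuts home use, and a 12-month usage figure requires survival to 12 months.

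For baseline factors the danger is milder but similar. A factor correlated with outcome only among HFOT users may simply mark people who would have done well on either treatment. At stake is a listed secondary outcome and a planned paper that could take prognosis or tolerance for response to HFOT.

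**Working it through.** **1. The plan's own figure.** Sample size {14} gives 270 people with COPD, hazard ratio 0.67, 1-year event rate 0.74, 80% power and two-sided alpha 0.05.

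- Schoenfeld: 4 × (1.960 + 0.842)² / (ln 0.67)² = 196 events; 196 / 0.74 = 265 people.
- Freedman: (1.960 + 0.842)² × (1.67 / 0.33)² gives 202 events after rounding up; 202 / 0.74 = 273 people.

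Both are close to 270 when 0.74 is read as the overall rate. The figure is not in dispute. It supplies the event counts below.

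**2. Assumptions not in the document.** A binary baseline marker present in half the participants multiplies the event hazard by 1.5 or 2.0 equally in both arms. It is purely prognostic and does not modify the effect of HFOT. The calculation concerns baseline markers; it does not quantify the bias in a usage-time association.

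**3. Marker tested within the HFOT arm only.** Here 0.74 is read as the control-arm rate, which gives the fewer HFOT-arm events.

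- HFOT event rate: 1 − (1 − 0.74)^0.67 = 0.594.
- Events: 135 × 0.594 ≈ 80.
- Standard error of the log hazard ratio for a 50:50 marker: 2 / √80 = 0.224.
- Marker hazard ratio 2.0: Φ(0.693 / 0.224 − 1.96) = 0.87.
- Marker hazard ratio 1.5: Φ(0.405 / 0.224 − 1.96) = 0.44.

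**4. Check by simulation.** There were 20,000 replicates per scenario, with 135 per arm, exponential times and censoring at 1 year. The 0.74 rate was placed midway between the arms on the log-hazard scale. Marker hazard ratios of 0.67 and 0.5 are about the inverses of 1.5 and 2.0.

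| Marker HR | Treatment HR | Significant, HFOT arm only | Significant, interaction |
|---|---|---|---|
| 1.0 | 1.0 | 5.2% | 5.1% |
| 1.0 | 0.67 | 4.8% | 5.0% |
| 0.67 | 1.0 | 51.4% | 5.1% |
| 0.67 | 0.67 | 47.1% | 5.2% |
| 0.5 | 1.0 | 93.0% | 5.1% |
| 0.5 | 0.67 | 90.7% | 5.0% |

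The within-arm rates exceed those in step 3 because this reading gives more HFOT-arm events. With treatment hazard ratio 0.67 the rate is 1 − exp(−1.347 × √0.67) = 0.668, or about 90 events. The interaction test keeps its nominal 5% throughout.

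**5. What the interaction test can detect.** With 270 × 0.74 ≈ 200 events and a 50:50 marker, the standard error of the log ratio of hazard ratios is √(16 / 199.8) = 0.283.

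- Ratio 0.67: Φ(0.400 / 0.283 − 1.96) = 0.29.
- Ratio 0.5: Φ(0.693 / 0.283 − 1.96) = 0.69.
- Ratio detectable with 80% power: exp(−2.80 × 0.283) = 0.45.

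If 0.74 is the control rate instead, total events are 270 × (0.74 + 0.594) / 2 ≈ 180, the standard error is √(16 / 180) = 0.298, and power at a ratio of 0.67 is 0.27. The conclusion is the same.

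**The case against.** The strongest reply is that no passage says the analysis will be confined to the HFOT arm. Outcomes {12} makes analysis by randomised group primary for everything, Statistical methods {20a} speaks of between-group regression, and a SAP is promised before each secondary analysis. The word correlational occurs in a list of planned papers, not in the methods, and does not exclude interaction models. For baseline factors this largely stands: the article names none for this outcome, a SAP may specify the right model, and the absence of that detail from an article is not itself a fault.

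It does not rescue usage time. That factor is named in the outcome itself, and no treatment-by-factor term can be formed for it.

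A reader might infer three stronger things that the document does not support.

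- **That prognostic factors will be reported as identifying who gains from HFOT.** This predicts a future paper. The outcome speaks only of association, and the within-arm analysis is a risk, not a stated plan.
- **That this paper will set selection criteria in guidelines.** The expectation of guideline uptake is stated for the study's results as a whole, not for this paper.
- **That usage time should be removed from the analyses.** It is deliberately collected, and after the pilot experience its relation to outcome is a fair exploratory question. The trouble lies in reading it as a predictor of benefit.

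**Conclusion.** The point holds for usage time as written: its correlation with outcome among HFOT users cannot be interpreted as benefit. For baseline factors it holds as a risk, which becomes real only if they are examined in the HFOT arm alone. The rates of about 44% to 87% against 5% are conditional on such an analysis, and on the assumed 50:50 prevalence and marker hazard ratios of 1.5 to 2.0. Reading 0.74 as the overall rate raises them somewhat. The pilot shows that use is self-selected, but procedures were changed afterwards, so it does not tell us how common stopping will be in the main phase. One secondary outcome and one planned paper are affected; the primary analysis and the sample size of 270 are not. The point deserves correction before that analysis is specified.

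**What to change.** 1. Reword the item in Outcomes {12}, and the matching paper in Dissemination plans {31a}, as baseline factors that modify the effect of HFOT. Define net clinical benefit, or name the outcomes on which modification will be assessed.
2. State that modification is estimated across both randomised arms with treatment-by-factor interaction terms, reported with confidence intervals and labelled exploratory.
3. Take usage time out of the predictors of benefit. Report its associations with outcome as descriptive only, or with a causal method prespecified in the SAP together with its assumptions.

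The cost is wording in the protocol and SAP. The data are already being collected, and the trial is still recruiting. The drawback is low power: about 29% for a ratio of hazard ratios of 0.67 with about 200 events, so fewer predictors will be claimed.
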